## Abstract

**Background:**

Currently, feasible medical treatments are hitherto not satisfying to relieve pSS symptoms, which concerns numbers of clinical doctors. Acupuncture seems to be an alternative to treat pSS and conduces to good symptomatic results. However further research is necessary. This trial is to investigate the efficacy of acupuncture on improving the key symptoms of pSS, which are dryness, pain and fatigue (DPF).

**Methods & Design:**

The study is designed as a randomized controlled trial of two arms with a single centre. We compare acupuncture with sham acupuncture on symptomatic improvements of pSS. A total of 120 pSS patients, aged at least 18, with DPF, will be randomly assigned to acupuncture or sham acupuncture groups, where they will have needle intervention for 8 weeks with 16 weeks of follow-up. Subjects will be assessed each time before interventions during the 8-week intervention, in week 8 after all interventions and in week 12, 16, 20 and 24 for follow-up with different measurements. The primary outcome are the proportions of subjects that have 30% or greater reduction in at least 2 out of 3 items of DPF in Numeric Analog Scale (NAS) scores (0 = the best, 10 = the severest), calculated between the baseline and the average scores of week 2 to 8. The secondary outcome are related to individual items of NAS scores, EULAR Sjögren’s Syndrome Patient Reported Index (ESSPRI), EULAR Sjögren’s Syndrome Disease Activity Index (ESSDAI), Schirmer test score and unstimulated salivary flow, serum Immunoglobulin G, A and M levels, Medical Outcome Study Short Form 36 Short-Form Health Survey (SF-36), Salivary glands ultrasounds, Hospital Anxiety and Depression (HAD) scale score. The secondary outcome scores are to be collected at baseline, in week 8, 16, and 24. Besides, individual items of NAS will also be collected in week 12 and 20. Moreover, subjects’ satisfaction and the proportion of the subjects who identified their allocation will also be measured and analyzed.

**Discussion:**

This study will be the first randomized and controlled pilot trial of acupuncture on alleviating the symptoms of pSS with relatively long-term follow-up. The result of the study might offer a new option to treat pSS and might be a clinical proof that acupuncture has beneficial effects on pSS.

**Trial registration:**

ClinicalTrials.gov: NCT02691377 (February 20, 2016)

## Background

Primary Sjögren’s syndrome (pSS) is a systematic autoimmune disease characterized by high lymphocytic infiltration in the exocrine glands such as salivary and lacrimal gland. The incidence in different populations varies from 0.5 to 2% [1]. There is a variety of clinical manifestations in pSS [2], in which, dryness, pain and fatigue (DPF) are considered as the 3 most urgent symptoms, and they affect patients quite much [3].

Current available medical treatments for pSS may lead to either serious adverse side effects, or failure to relieve symptoms. Thus, Bio-agents (e.g. rituximab, abatacept, belimumab), immunosuppression (e.g. and azathioprine, cyclophosphamide, mycophenolate mofetil) or corticosteroids should be cautiously applied clinically because of their safety and cost-effectiveness, although life-threatening complications after taking them are rarely seen. Even the most frequently prescribed medicine for pSS [4, 5], hydroxychloroquine, does not alleviate symptoms compared to the sham in a recent research [6]. Thus, some patients resort to complementary and alternative medicine, for example, acupuncture.

Acupuncture, as a non-pharmacologic therapy from Traditional Chinese Medicine, has been applied in a variety of disorders, including clinical symptoms of dryness [7]. Researches done in the past have shown the researchers’ recognition and expectation on acupuncture for dryness, and a research blank in “Acupuncture + Sjögren’s syndrome” as well [8, 9].

It seems that pSS patients have a good clinical response to acupuncture therapy in daily clinical practice, with acupoints and manipulations inherited from [name] [10], one of the National Masters of Traditional Chinese Medicine (no more than 10 people in China), who has contributed himself to treating and studying rheumatoid diseases by using herbs and acupuncture for over 50 years. Our previous research indicates that acupuncture performs in a synergy with a particular formula of herbs, with which patients relieve from dryness of mouths and eyes, pain and fatigue, and it improves the quality of lives of pSS patients (it’s a result from our recent study not long after finished, which has been accepted by a journal but hasn’t been published yet). However, there are still questions not settled yet, such as how indeed is the effect of acupuncture on relieving symptoms of pSS statistically; if acupuncture works, what kind of patients will be benefit from it; and if not, why do some of the patients think they have symptomatic improvement after acupuncture. This study is designed to answer these questions.

## Methods & Design

### Study design

The study is a single-centre, double blinding and 24-week randomized and controlled trial with two arms, in one of which, needles will be inserted into previously set acupoints while sham acupuncture for the other group. 120 patients with symptomatic pSS are randomly assigned to acupuncture or sham acupuncture groups in 1:1 ratio. Needles are administered 3 times a week for the first 4 weeks, twice a week for the second 4 weeks, with 16-week of follow-up. All the allocation, intervention, randomization and analysis, etc., will be conducted in Guang’anmen (GAM) Hospital. The primary outcome is the two proportions of subjects in the two groups that have 30% or greater reductions in NAS scores in at least 2 out of the 3 DPF items [6]. They are calculated between baseline and the average scores between week 2 and week 8. The secondary outcome are related to individual items of NAS score at baseline, 3 times a week in week 0 to 8, and once a week at week 12, 16, 20, and 24, with EULAR Sjögren’s Syndrome Patient Reported Index (ESSPRI), EULAR Sjögren’s Syndrome Disease Activity Index (ESSDAI), Schirmer Test Score and Unstimulated Salivary Flow, Medical Outcome Study Short Form 36 Short-Form Health Survey (SF-36), Salivary glands ultrasounds, Hospital Anxiety and Depression (HAD) scale score, at baseline, week 8, 16 and 24. During the 8-week intervention, data of the last 24 h is collected each time before the intervention. Since there are only twice a week in week 4 to 8 for intervention but 3 times for NAS collection, the extra one is collected by phone.

### Randomization and blinding

Subjects eligible for participation will be randomly assigned to one of the following study groups, using the randomization software SAS (Statistical Analysis System) 9.2.penetrating acupuncture: 60 subjectssham acupuncture: 60 subjects

The statisticians will randomize assignments using a sequence of number randomly generated by the SAS (Statistical Analysis System) 9.2, done by a third organization, a Statistical Department of State Standardized Traditional Chinese Medicine Pharmacology Clinic (SDSSTCMPC) granted by State Food and Drug Administration (SFDA). The sequence will be recorded and can be displayed when necessary. These assignments will be sent to a study member, who will put them into sealed, opaque envelopes with dates and signature labels over the seals. And this study member will not take part in any of patient interviews, acupuncture intervention, data collection, or statistical analysis.

Before eligible subjects are randomized into different groups, informed consent contract will be obtained from each participant and they will be interviewed to ensure their baseline data recorded. Then they will allocate and come to see the acupuncturist who will open the consecutive randomization envelope, and then apply acupuncture or sham one according to the assignment without informing the subjects of their assignments. As the only one knowing the group assignments of subjects, the acupuncturist will not participate in any of the interviewing, data collection, or statistical analysis. Every time before the intervention, except the first time, which is baseline, the subjects will come to the interviewing room where the case report form (CRF) with NAS scores will be filled with their feedback on NAS scores about last 24 h instead of a time point. After the intervention, the schedule for their acupuncture and interviewing for next time (including date and time) will be informed.

### Patients

#### Inclusion criteria

Age 18+To meet the American-European Consensus Group Criteria for primary Sjögren syndrome [11]Symptoms have been appearing for less than 5 years; signed a written informed consent formWithout taking pSS medicines, or have not been taking pSS medicines for at least 4 weeks before the recruitment, or have been taking the same kinds and doses of pSS medicines (non-steroidalanti-inflammatory drugs, NSAIDs; oral taken cortical hormone; pilocarpine; artificial eye liquid; herbal decoctions) for more than 4 weeks before the recruitment, or have been taking the same kinds and doses of other pSS medicines (tripterygium wilfordii; methotrexate; cyclophosphamide; cyclosporin; azathioprine; hydroxychloroquine sulfate) for more than 6 months before the recruitment.

#### Exclusion criteria

Secondary Sjogren syndromeHave been having serious systemic disorders recently (lymphoma; central nervous system, renal, or pulmonary involvement; myositis; or vasculitis) or severe renal or liver failureHave had acupuncture treatments in last 20 daysWith acupuncture contraindications (allergy to metals, skin lesions on relative acupoints, etc.)Subjects who participate in any other clinical trials in last 30 days before recruitmentCurrently or planning to be pregnant, or at risk of being pregnant without contraceptionSubjects with a physical or psychological problem, which may confound the trial results, interfere with other subject’s participation, or may make it risky to follow the investigators’ requirementsSubjects known for or persistent in drug or alcohol abuses

### Recruitment strategies

Patients will be recruited through a number of advertising strategies, with the information of physicians and the details and requirements of the trial. Posters in GAM Hospital, and advertisements on the online official medical medias, such as websites, Weibo (similar to twitter in China), and Wechat (similar to Facebook in China) of Rheumatology Department of GAM Hospital, will also be applied for recruitment. Also, another main recruiting way is that patients comes from outpatient service.

### Intervention

Since sham control is a useful method for determining the effectiveness of a therapy, we will choose a sham needle [12] that has a blunt tip and achieves no skin penetration. To apply the sham needles produces a good subject blinding effect, the reason of which is that they have a similar appearance to conventional acupuncture needles, however, without skin penetration. Also, we put plastic pads on the acupoints before to cover the areas so as to keep the patients blinded to if or not there’s penetration.

### Description of sham acupuncture

The sham needle is 0.30mm wide and 25mm long. It consists of an adhesive pad with a blunt tip (Fig. 1). The adhesive pad is made of a sterile cylindrical polyethylene foam (diameter 10mm and height 5mm) with a double-sided adhesive tape at the bottom. The adhesive pad has 2 functions: one is holding the sham needle on the acupoints when used in sham acupuncture and the other function is assisting the implementation of blinding when used in both sham and real acupuncture. In all, the only difference between normal and sham needles is that the sham ones tips are not tapering.

**Fig. 1 Fig1:**
[figure not shown]
The sham and real acupuncture we use in this study. **a**: sham acupuncture as control; b: real acupuncture. 1. needle handle; 2. needle body; 3. adhesive pad; 4. blunt tip; 5. Cutis

### Process of the intervention

All of the subjects will be told that we are going to evaluate the effects of “a new kind of acupuncture” researching on “deep penetrating needles and shallow penetrating needles” on pSS, without mentioning sham, pseudo or the penetration status. The experienced acupuncturist will be trained on the sham needles and will apply both the sham and real needles throughout the whole trial. Each time before the intervention, subjects will be asked to meet the interviewer in another room to provide their answers on CRF with the feelings of the last 24 h before the intervention, excluding the first intervention, whose data will be the baseline. Acupoints and manipulations are the same in 2 groups (Fig. 2), with bilateral Waiguan (SJ5) with reducing method; bilateral Zhaohai (KI6) with reinforcing method; Chengjiang (RN24), Lianquan (RN23), bilateral Taiyang (EX-HN5), bilateral Cuanzhu (BL2), bilateral Sizhukong (SJ23), and bilateral Jiache(ST6) with even method. During the manipulations, twirling, lifting, and thrusting to elicit Deqi or needle sensation (a composite of unique sensations interpreted as the flow of qi induced by acupuncture and essential for clinical efficacy [13]), will be applied, and the needles will be remained for 20 min. Subjects will receive acupuncture or sham acupuncture 3 times a week for the first 4 weeks, twice a week for the second 4 weeks, followed by 16 weeks of observation without treatments. For week 4 to 8, intervention will only be conducted twice a week, therefore one more interview for NAS scores every week will be on the phone.

**Fig. 2 Fig2:**
[figure not shown]
The acupoints we picked in this study and their indications

#### Primary outcome

The numeric analog scale (NAS) [14] scores of DPF (0 = the best, 10 = the severest) will be measured at the baseline, three times a week in week 1 to 8, and once a week in week 12, 16, 20, and 24. By the comparison of the average scores of week 2 to 8 with those of the baseline of the two arms, the proportions of the subjects in two groups that have 30% or greater reductions in NAS scores in at least 2 out of 3 DPF items, will be the primary outcome.

Subjects will be asked to provide every NAS score based on the overall situation of the past 24 h [15] rather than a point of time. And we will collect NAS scores 3 times a week in week 1 to 8 (24 times in total).

The mentioned outcome measurements will be assessed at the marked time points respectively (Fig. 3).

**Fig. 3 Fig3:**
[figure not shown]
Trial flow & study design. General information = age, sex, weight, time when symptoms emerge, time when diagnosed, anti-SSA antibodies, abnormal Schirmer test results, decreased unstimulated salivary flow, previous systemic involvement, previous treatment with another immunosuppressant, current systemic involvement. 1st outcome = numeric analog scale (NAS) (Dryness, Pain and Fatigue). 2nd outcome = EULAR Sjogren Syndrome Patient Reported Index (ESSPRI), EULAR Sjogren Syndrome Disease Activity Index (ESSDAI), Medical Outcome Study Short From 36 Short-Form Health Survey (SF-36), Hospital Anxiety and Depression (HAD), Serum Immunoglobulin (IgG), IgA and IgM, Schirner test score and unstimulated salivary flow, salivary glands untrasounds

#### Secondary outcome

Secondary outcomes include each items of NAS scores from week 0 to 8. These items will be measured individually at baseline, 3 times a week in week 1 to 8, once a week in week 12, 16, 20, 24. The secondary outcomes also include:EULAR Sjögren’s Syndrome Patient Reported Index (ESSPRI) [16] is a very simple index completed by patients to measure symptoms in pSS. With good construction validity, it is used as an outcome measure in clinical trials. There is a 0–10 numerical scale for each of the four domains, dryness, discomfort (including pain), global fatigue and mental fatigue, which are gathered to form the ESSPRI. For sicca features, six components were identified, which are ocular, oral, skin, nasal, tracheal and vaginal.EULAR Sjögren’s Syndrome Disease Activity Index (ESSDAI) [17, 18] is a clinical index completed by physicians to measure disease activity in patients with pSS. There are 12 organ-specific ‘domains’ contributing to disease activity. For each domain, features of disease activity are classified into three or four levels according to their severity.Schirmer test score and unstimulated salivary flow [19]: these two tests are the objective reflection to the lacrimal gland and salivary glands, the results of which can be greatly impacted by the operator. Thus, there will be a technician performing these two tests during the whole trial to maintain the homogeneity of the operation.Serum Immunoglobulin G, A, M levels [20]: Immunoglobulin G (IgG) is commonly believed in clinic a reflection of pSS symptom activities and a study shows weak associations between increasing fatigue and serum IgG, and the pro-inflammatory cytokine interleukin-17 (IL-17), were observed.Medical Outcome Study Short Form 36 Short-Form Health Survey (SF-36) [21, 22] is a self-administered questionnaire with 36 items, which assesses the concepts of physical function, role limitations due to physical problems, social function, body pain, general mental health, role limitations due to emotional problems, vitality, and general health perceptions. Note that both physical and mental component summaries can be combined. Scores range from 0 to 100, with higher scores indicating better health status [23].Salivary glands ultrasounds [24]: image of salivary glands structures. This can be quantified by a form based on different features.Hospital Anxiety and Depression (HAD) scale score [25]: A self-assessment scale which has been developed and found as a reliable instrument for detecting states of depression and anxiety in the setting of an hospital medical outpatient clinic.

For the secondary outcomes listed above, the measurements are conducted at baseline, in week 8, 16 and 24. Besides, the satisfaction of patients in two groups and the proportion of the subjects who identified their allocation will be measured in week 8.

Additionally, we will assess the patients’ satisfaction in week 24 by two questions. 1) “Would you like to come for more treatments or recommend it to your friends/relatives if they have similar symptoms?” The answer will be either “yes” or “no”. 2) "What is your feeling for the series of treatment?” The answers will include “excellent”, “good”, “satisfactory”, “It’s okay” and “poor”. The difference in satisfaction between two groups will be analyzed.

To evaluate the success rate of blinding, we will ask subjects in week 8 “how deep do you think the needles went into your skin?” The answer will be “deep”, “shallow” or “no penetration”. The subjects in the two groups whose answers are either “deep” or “shallow” will be considered to be blinded successfully, while “no penetration” unsuccessfully, and the proportions of them are going to be compared.

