### Statistical analysis

For data analysis, statisticians and investigators will be blinded for the patients’ allocation. Statistical analysis will be performed using SPSS Ver.20 (SPSS Inc., Chicago, IL, USA) software. Enumeration data will be described as frequency and composition ratio. Continuous data will be presented by Mean ± Standard Deviation (M ± SD) if they meet normal distribution, otherwise they will be expressed as Medians ± Interquartile Range (M ± IQR). Categorical data will be presented by frequency and percentage. The analyses of efficacy will be based on the intention-to-treat (ITT) analysis set, which was defined as patients who receive at least one treatment. Missing data for the primary outcome will be treated by multiple imputation under chained equation, with m = 50 imputations. The covariates used to generate the multiple imputed data sets are age, sex, NAS scores of DPF, ESSDAI, ESSPRI, salivary flow rate, and Schirmer test score. For comparison with the baseline, a repeated measures data analysis of variance (ANOVA) or Wilcoxon signed rank test will be used for continuous data, whereas Chi-square test or Fisher exact test will be used for categorical data. In terms of comparison between the two groups, Chi-square test or Fisher exact test will be used for primary outcomes. For secondary outcomes, the analysis of covariance (ANCOVA) will be used if the residual are normal distributed, otherwise Wilcoxon rank sum test will be applied. To access the success of blinding, the proportion of subjects who are successfully blinded will be compared by Chi-square test or Fisher exact test. And nonparametric test will be used to analyze satisfaction. *P* <0.05 with two-tailed test indicates statistical significance.

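### Satisfaction question 1 puts two questions under one yes/no answer, so its planned between-arm comparison cannot be read as either

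*Protocol article*

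**What the plan says.** The section on secondary outcomes in the protocol article schedules satisfaction twice. For the end of treatment it says that "the satisfaction of patients in two groups and the proportion of the subjects who identified their allocation will be measured in week 8". The next paragraph adds a further assessment of "satisfaction in week 24 by two questions".

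The first question reads "Would you like to come for more treatments or recommend it to your friends/relatives if they have similar symptoms", and its answer format is binary: "The answer will be either “yes” or “no". The second asks for the patient's feeling about the treatment series: "The answers will include “excellent”, “good”, “satisfactory”, “It’s okay” and “poor".

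The comparison is stated as "The difference in satisfaction between two groups will be analyzed", with no time point named. The section on statistical analysis adds only that a "nonparametric test will be used to analyze satisfaction".

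**The concern.** Question 1 covers two separate judgements. One is whether the patient personally wants more treatment, which depends on remaining symptoms, travel and time. The other is whether the patient thinks well enough of the treatment to recommend it. With 'or' between them, a patient who holds either view answers 'yes'. Read literally, only a 'no' is clear: it means neither.

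The between-arm comparison of this item is therefore a comparison of a mixture. If the arms differ, one cannot say on what. If they do not differ, one cannot say that they agree on both parts. Once the answers are collected, the two parts cannot be separated.

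Two smaller matters go with this. No main time point is named for the comparison although two assessments are scheduled. Question 2 also has only one clearly unfavourable answer among five.

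**Working it through.** **Inputs.** The wording, the binary format and the five answer levels come from the section on secondary outcomes. The documents give no expected answer rates for satisfaction, so there is no figure of the plan to reproduce. The sample size rests on the primary outcome and has no bearing here. All rates below are assumptions, chosen to show the range.

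**Question 1.** Let *a* be the proportion who want more treatment and *b* the proportion who would recommend it. Under the literal 'or':

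- answers independent: P(yes) = 1 − (1 − *a*)(1 − *b*)
- answers fully overlapping (the smaller group lies inside the larger): P(yes) = max(*a*, *b*)

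For example, take *a* = 60% vs 40% and *b* = 70% in both arms. Independence gives 1 − 0.40 × 0.30 = 0.88 and 1 − 0.60 × 0.30 = 0.82, a difference of 6 points. With equal *b* the general result is 20 × (1 − *b*) points.

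| Wants more, % | Recommends, % | 'Yes' if independent, % | Difference | 'Yes' if overlapping, % | Difference |
|---|---|---|---|---|---|
| 60 vs 40 | 30 vs 30 | 72 vs 58 | 14 | 60 vs 40 | 20 |
| 60 vs 40 | 50 vs 50 | 80 vs 70 | 10 | 60 vs 50 | 10 |
| 60 vs 40 | 70 vs 70 | 88 vs 82 | 6 | 70 vs 70 | 0 |
| 60 vs 40 | 90 vs 90 | 96 vs 94 | 2 | 90 vs 90 | 0 |
| 60 vs 40 | 60 vs 40 | 84 vs 64 | 20 | 60 vs 40 | 20 |
| 20 vs 10 | 20 vs 10 | 36 vs 19 | 17 | 20 vs 10 | 10 |

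The combined item can thus shrink a true difference (first four rows, independent answers), preserve it (fifth row) or enlarge it (last row, independent: 17 points from two differences of 10). Which case applies cannot be known from the documents, nor from the combined answers once collected.

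**Question 2.** Does the unbalanced label set weaken the comparison? A rank test uses the order of the answers, not how favourable the labels sound. A simulated Wilcoxon rank-sum test (51 per arm, taken as 60 × 0.85; 4,000 runs; assumed latent shifts of 0.4 and 0.6 SD) gave these powers:

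- evenly centred categories: 0.46 and 0.81
- answers spread over the favourable options (poor 10%, okay 20%, satisfactory 25%, good 30%, excellent 15%): 0.48 and 0.80
- answers crowded at the low end (30, 30, 20, 15, 5% in the same order): 0.48 and 0.81
- a ceiling with 40% in the top level, on any five-level scale: 0.42 and 0.74

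The simulation error is about √(0.5 × 0.5 / 4000) = 0.008. The loss comes from a ceiling in the answers, not from the labels.

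**Timing.** Treatment ends at week 8 and is "followed by 16 weeks of observation without treatments", so the second assessment looks back 24 − 8 = 16 weeks. The first has no such gap.

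**The case against.** The strongest case on the other side is that this is an ancillary item in a condensed journal article, and that most of what one might say against it goes beyond the text. Much of that stands.

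- *Satisfaction is asked only at week 24, and too late.* A reader might infer this because both printed questions are tied to week 24. The text does not support it. Week 8 is scheduled, and week 24 is introduced as an addition to it. The week 8 item may stand in the full protocol or the case report form, which are not shown. An overall rating at week 24 also suits the stated interest in longer-term effects.
- *The combined item hides differences.* The table shows that this depends on the assumed rates. The 6-point result arises because recommending was set equal in both arms. Independence is also doubtful, since the two answers are likely to be correlated.
- *The answer scale of question 2 makes the comparison insensitive.* The simulation does not show this.
- *Up to 15% of week 24 answers will be missing.* The 15% is the drop-out assumption used to enlarge the sample size for the primary outcome. It is not a forecast for this questionnaire.

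None of this answers the wording of question 1. It is printed in full, it joins two ideas under one answer, and a between-arm analysis of satisfaction is promised.

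**Conclusion.** The point holds for question 1: its between-arm comparison cannot be interpreted as a difference in wanting more treatment or as a difference in recommending it. This follows from the printed wording and needs no assumption about rates. The effect on the size of an observed difference is undetermined. In the illustrations, a 20-point difference in wanting more treatment shows as 0 to 20 points, and two 10-point differences show as 10 to 17.

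The unbalanced scale of question 2 affects description only: a mildly dissatisfied patient has no fitting answer, so reported percentages may look favourable in both arms. A late or insensitive comparison is not shown. Severity is minor. The primary outcome and the sample size are not affected.

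**What to change.** - Split question 1 into two yes/no questions: would you want more of this treatment, and would you recommend it to friends or relatives with similar symptoms. Report and compare each separately.
- Use the same questions at both scheduled assessments, week 8 and week 24, and state which of the two is the main between-arm comparison.
- Optional: give question 2 a symmetric set of answers that includes a mildly unfavourable option. This improves the description and should not be presented as a gain in power.

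The cost is one extra yes/no item at each assessment, and one more ancillary comparison to report. The change has to be made before the questionnaire is used, because merged answers cannot be separated afterwards.
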